## Abstract

**Background:**

Loneliness has become a global public health problem associated with serious diseases and early mortality. A promising non-medical group-based strategy to address loneliness is nature-based social prescribing (NBSP). The aim of this paper is to describe the design of a health economic evaluation of NBSP interventions alongside trials conducted in the EU H2020 project RECETAS.

**Methods:**

The health economic evaluation will be conducted alongside the RECETAS randomized controlled trials in Barcelona, Prague, and Helsinki, and comprises cost-utility, cost-effectiveness, and cost-capability analyses. Depending on each study site’s specific setting and target population, the economic evaluation will be performed from a societal and/or a healthcare perspective. NBSP interventions, which include referring lonely people to participate in activities organized in a natural environment and providing a selection of nearby nature-based community resources, will be evaluated against usual care. Effectiveness measures include health-related quality of life assessed with the EQ-5D-5 L questionnaire, changes in loneliness obtained from the De Jong Gierveld Loneliness Scale, and capability derived from the ICECAP-A questionnaire. Direct healthcare costs, indirect and informal costs as well as the actual costs of the intervention will be included. The data on health outcome and health care resource utilization will be collected at baseline and at three-, six- and twelve-months follow-up of the trial. The incremental cost-utility ratio, incremental cost-effectiveness ratio, and incremental cost-capability ratio will be calculated. National willingness-to-pay thresholds will be applied where available.

**Discussion:**

Our study protocol provides a systematic framework designed prospectively for conducting the health economic evaluation of the NBSP intervention for people suffering from loneliness. Through the publication of the study protocol, the research process becomes transparent and reproducible. This reduces bias when interpreting the results and conclusions and ensures good evidence-based practice, so that decision makers can provide evidence-based recommendations without arbitrariness to support NBSP implementation.

**Trial registration:**

Barcelona (Spain) trial ClinicalTrials.gov, ID NCT05488496. Registered 29 July 2022 Prague (Czech Republic) trial ClinicalTrials.gov, ID NCT05522140. Registered August 25, 2022 Helsinki (Finland) trial ClinicalTrials.gov, ID NCT05507684. Registered August 12, 2022.

## Background

Loneliness has emerged as a significant public health concern, as highlighted by the United States Surgeon General [name] in 2023, who referred to this issue as an epidemic [1]. A recent report from the World Health Organization reinforces this assessment, confirming that loneliness is a growing public health issue on a global scale with considerable social and economic expenses [2].

Loneliness is defined as “the unpleasant experience that occurs when a person’s network of social relations is deficient in some important way, either quantitatively or qualitatively” [3]. Despite the fact that maintaining social contact has never been easier due to technology, the prevalence of loneliness remains high around the world [4, 5]. Loneliness transcends geographical borders, affects all generations, and is related to serious diseases such as a cognitive decline or dementia [6], diabetes [7], depression and anxiety or cardiovascular diseases [8, 9] and can lead to early mortality [10–12].

Traditionally, social support has been identified as an important determinant in alleviating loneliness [13]. One upcoming idea for addressing loneliness as a global public health problem is social prescribing (SP), defined as a healthcare approach that connects individuals to non-medical community resources and activities to improve their overall well-being [14]. As a subtype of SP, nature-based social prescribing (NBSP), which includes green and blue social prescribing, focuses on individual and/or group-based actions related to nature, such as gardening, fishing, bird watching or hiking [15, 16].

While evidence on the effectiveness of NBSP in reducing loneliness is growing, there is a clear research gap regarding health economic evaluations of such interventions [17, 18]. In particular, there is a lack of cost-utility, cost-effectiveness, and cost-capability studies of NBSP interventions conducted alongside randomized controlled trials (RCTs) [19]. In times of restricted healthcare budgets, more evidence on resource utilization, costs, and cost effectiveness of new health interventions is necessary [20]. There is rising demand to assess cost-effectiveness alongside the trial next to the effectiveness of an intervention, to inform policy and decision makers about whether an intervention provides good value for the resources invested. Economic evaluations conducted alongside the trial are considered among best practice methods for systematic analysis of cost effectiveness [21]. RCTs can facilitate health economic evaluations by collecting data on the costs of the intervention and assessing the trade-offs between costs and effectiveness [22].

This study protocol is framed within the RECETAS (Re-imagining Environments for Connection and Engagement: Testing Actions for Social Prescribing in Natural Spaces) study [23]. The aim of this article is to present a site-specific study protocol for the health economic evaluations conducted alongside three RECETAS RCTs to evaluate whether NBSP is cost effective as a loneliness-reduction strategy.

## Methods

This methods section describes the framework elements and steps of our health economic evaluation, including: the RECETAS trial design, study setting and population, interventions and comparators, measurement and valuation of outcomes/ benefits, resource utilization and costs, statistical analysis, sample size and missing data, health economic evaluation designs of the cost-utility analysis (CUA), cost-effectiveness analysis (CEA), cost-capability analysis (CCA), and responder analysis, as well as sensitivity and scenario analyses.

### RECETAS trial design

RECETAS is an EU H2020 project (No 945095) that specifically addresses the social determinants of health and analyzes the impact of NBSP interventions on outcomes including loneliness, health-related quality of life and capability well-being, across three registered RCT study sites, and examines its qualitative aspects in three pre-post observational study sites [24]. The study protocol for the RECETAS trials describing the eligibility criteria and a logic model explaining the RECETAS project and the NBSP interventions has been published earlier [23, 24]. The RECETAS project addresses loneliness and aims to assess effectiveness, costs, and cost effectiveness of NBSP on loneliness in six different study sites across Europe, Latin America, and Australia [24]. Three pre-post observational studies in Cuenca (Ecuador), Marseille (France), and Melbourne (Australia) consider the relationship between NBSP and loneliness using qualitative methods [25]. Three randomized controlled trials (RCTs) are conducted in Barcelona (Spain), Prague (Czech Republic), and Helsinki (Finland). Three separate and site-specific health economic evaluations of NBSP for Barcelona, Prague, and Helsinki will be performed based on the data collected in the respective RCTs [23, 26]. The effectiveness and cost effectiveness of the two strategies (NBSP intervention vs. control group) within the RECETAS project will be assessed after three months at the end of a NBSP intervention, and at six-, and twelve-months post-randomization. The health economic evaluations alongside the trials will quantify the resources utilized in both arms and the additional costs and incremental health outcomes of NBSP compared to usual care from a societal and/or healthcare perspective and will include incremental cost-utility, cost-effectiveness, and cost-capability analyses.

International guidelines, such as the International Society for Health Economics and Outcomes Research (ISPOR) Good Research Practices Task Force Report on Cost-effectiveness Analysis alongside Clinical Trials II [27], Methods for Health Economic Evaluations - A Guideline Based on Current Practices in Europe [28], and the Consolidated Health Economic Evaluation Reporting Standards 2022 (CHEERS 2022) [29] will be followed for analyzing and reporting the results. Each intervention site obtained ethical approval by the respective Ethics and Research Committees (Barcelona: Research Ethics Committee at UVic-UCC, registration number 2014/2022 on 28 June 2022; Primary Health Care Research Institute of Catalonia, registration number 22/170-P on 02 August 2022; The Ethics Committee for Research with Medicines at IRIS-CC, registration number 23/016 on 11 October 2023; Prague: Ethics Committee of the Faculty of Humanities, Charles University on 28 June 2022; Helsinki: University Hospital Ethics Committee (No HUS/119/2022), Social Services and Health Care of the City of Helsinki on 13 June 2022) [23]. Ethical approval at UMIT TIROL – University for Health Sciences and Technology was also obtained from the Research Committee for Scientific Ethical Questions (registration number: 3274 on 19 June 2023).

### Study setting and population

The study population of our health economic evaluations alongside the trial depends on the three different study sites: In Barcelona, adults over 18 years living in socio-economically vulnerable areas suffering from loneliness are selected (RECETAS-BCN trial) [23, 25]. In Prague, older people (60+) with a risk of social isolation and loneliness are included (RECETAS-PRG trial). For the study carried out in Helsinki, older people (55+) living in local assisted living facilities (retirement homes), some with mild-moderate cognitive impairment are included (RECETAS-HLSNK trial) [25].

### Interventions and comparators

In all three RCTs (Barcelona, Prague, and Helsinki), participants are randomized to an intervention or control arm. Detailed descriptions of both arms have been published previously [23, 30]. Briefly, in the intervention arm, participants participate in the “Friends in Nature” (FIN) intervention, an adaptation from the Circle of Friends^®^ methodology developed by the University of Helsinki [30], “customized to the specific target population in each trial and with a focus on nature-based activities” [23]. Two trained facilitators are assigned to each group to support the group dynamics by fostering empowerment and, at the end of the group process, independence from the facilitator. The training and mentoring process of the facilitators based on the Circle of Friends^®^ methodology has also been described previously [23, 30]. In the first session, an individualized one-to-one interview with the facilitators is conducted in Barcelona and Prague. Individuals are then allocated to take part in a program of weekly nature-based group activities (5–12 people) for nine sessions [23]. The activities vary from week to week, and include a combination of strategies promoting empowerment, social connectiveness, and participation in nature-based activities. The group stays together, and they discuss and decide on the activities. During this time, the facilitators keep a diary, instruct the group, assure connectivity, and assist in ensuring compliance. The control group receives usual care (UC). In Barcelona and Prague, UC consist of an individual NBSP interview at which participants receive a menu of nearby nature-based community resources to utilize individually, without further support [23]. Potential uptake of nature-based activities following the interview will not be considered in our health economic evaluations. In Helsinki, control participants receive normal care, which includes socializing in their ward, occasional recreational activities and some outdoor activities. Importantly, they do not participate in any further organized activities and receive no support from the FIN group or the facilitators.

### Measurement and valuation of outcomes/ benefits

For the health economic evaluation in Barcelona and Prague, the effectiveness of the intervention will be measured by comparing health-related quality of life (HRQoL), loneliness, and capability against the control group. Capabilities are applied to measure wellbeing beyond health [31]. In Helsinki, the effectiveness of the intervention will be assessed by comparing HRQoL and loneliness only. In Helsinki, by agreement with the responsible trial partners, capabilities will not be assessed as a large proportion of the participants may be cognitively unable to respond reliably and no Finnish translation of the respective measurement instrument (i.e., ICECAP-A) is available.

A cost-utility, cost-effectiveness, and in Barcelona and Prague, a cost-capability analysis will be performed. In addition, a responder analysis will be conducted [32, 33]. Results will be interpreted with priority given first to the cost-utility analysis, followed by the cost-effectiveness analysis, the cost-capability analysis, and finally the responder analysis.

Table 1 summarizes the measured health outcomes, instruments applied, time points, study sites, where the outcome will be measured, and data sources.

**Table 1 Tab1:** Overview of measured health outcomes

Health Outcome	Instrument	Time Points	Study Sites	Data Source
Health-related quality of life	EQ-5D-5L	t0, t1, t2, t3	Barcelona, Prague, Helsinki	Trial (Self-reported outcomes, proxy version by facilitators/ study nurses)
Loneliness	De Jong Gierveld Loneliness Scale	t0, t1, t2, t3	Barcelona, Prague, Helsinki	Trial (Self-reported outcomes)
Capability	ICECAP-A	t0, t1, t2, t3	Barcelona, Prague	Trial (Self-reported outcomes)

*EQ-5D-5L* European Quality of Life 5 Dimensions 5 Level, *ICECAP-A* ICEpop CAPability measure for Adults t0: baseline, t1: after 3 months; t2: after 6 months; t3: after 12 months

For the primary cost-utility analysis (CUA), HRQoL will be measured by the generic quality-of-life instrument EQ-5D-5L [34, 35], which will be translated into utilities using national tariffs where available. The EQ-5D-5L is an established instrument to assess HRQoL and recommended to be used in health economic evaluations [36, 37]. For countries without an EQ-5D-5L tariff but with a value set for the three-level version of the EQ-5D, the mapping methodology will be applied [38]. Where no value set exists for the EQ-5D-5L in the country concerned, the most appropriate European value set will be chosen [38]. Table 2 gives an overview of the applied valuation approaches for HRQoL For Spain, the EQ-5D-5L is a valid instrument to measure perceived health [39] and a country-specific value set is available to calculate health utility scores [40]. For the Czech Republic, no value set exists so far and national guidelines recommend to use the UK tariff [41, 42] as done in a previous study [43]. However, there is no empirical justification for designating a particular tariff as the default and it is advised to apply a value set from a country that is comparable [38]. A recent study by Laszewska et al., 2022 developed supra-national value sets based on five criteria “cultural differences, religion, language, healthcare system typology, healthcare system financing and sociodemographic aspects” [44]. The Czech Republic was identified to have strong links to Poland, for which a EQ-5D-5L value set exists [45], within these five criteria [44]. For Finland, only a value set for the EQ-5D-3L exists [46], which can be mapped to the five-level version using the crosswalk approach [47, 48]. The study by Laszewska et al., 2022 grouped Finland within the Nordic cluster of countries, for which the Danish value set was the only one available [44]. In the absence of a national value set, the Danish EQ-5D-5L value set, next to the UK value set, has been commonly used as a proxy in Finnish economic evaluation studies. If, during the duration of the study, a more relevant value set for one of the participating countries becomes available, this will be used.

**Table 2 Tab2:** Overview of applied valuation approaches for health-related quality of life

Study Site	Instrument for HRQoL	Value Set	Source
Barcelona, Spain	EQ-5D-5L	Spain	Ramos-Goñi, Craig [40]
Prague, Czech Republic	EQ-5D-5L	Poland	Golicki, Jakubczyk [45]
Helsinki, Finland	EQ-5D-5L	Denmark	Jensen, Sorensen [49]

*EQ-5D-5L* European Quality of Life 5 Dimensions 5 Level, *HRQoL* Health-related quality of life

The EQ-5D-5L questionnaire assesses five dimensions mobility, self-care, usual activities, pain/ discomfort, and anxiety/ depression with respectively five levels to be indicated by the respondents (no problems, slight problems, moderate problems, severe problems, and extreme problems) resulting in 3,125 health states [50]. A health-state utility value (HSUV) is attached to each of these specific health states. Utilities are a preference-based single number index ranging between 0 (dead) and 1 (perfect health). Quality-adjusted life years (QALYs) are derived by weighting the time in a health state by the HSUV, that is multiplying the HSUV with the time each individual is in the health state [50] and calculating the area under the empirical utility curve for the exact time until the final follow-up after twelve months or death. The EQ-5D-5L questionnaire will be distributed to and filled out by the participants in Barcelona and Prague. However, in Helsinki, the EQ-5D-5L questionnaire will be used as a proxy version filled out by facilitators or study nurses. The proxy questionnaire is provided for participants who are unable to answer the original questionnaire due to cognitive impairments.

Loneliness will be measured with the validated 11-item De Jong Gierveld Loneliness Scale (DJGLS), which offers three or five response possibilities [51, 52]. The overall score ranges from 0 to 11 and categorizes loneliness into three stages: 0–2: not lonely, 3–8: moderately lonely, 9–11: strongly lonely [52]. Loneliness will be assessed in different time intervals between baseline (t0), at the end of the NBSP intervention after three months (t1), at the end of a maintenance phase after six months (t2), and at the end of the follow-up period of the project after twelve months (t3). Loneliness-free days (LFD) will be calculated by transforming the DJGLS score from 0 to 11 to a loneliness value between 0 and 1. A score of 0–2 (meaning that an individual feels not lonely) on the DJGLS will be assigned with a value of 1 (having a “Loneliness-free day”), whereas a score of 9–11 (meaning that an individual feels strongly lonely) will be assigned with a value of 0 (having a “Loneliness day”). Days with intermediate scores of 3 to 8 (meaning that an individual feels moderately lonely) will be assigned a value between 1 (“Loneliness-free day”) and 0 (“Loneliness day”) by linear interpolation. This approach is in line with the approach used by a previous study using depression-free days as health outcome [53]. The number of LFD over time will then be calculated by multiplying the loneliness value (from 0 to 1) with the days (e.g., 90, 180) in this loneliness state [54]. A hypothetical example with a graphical representation of the LFD calculation can be found in the Appendix A1. The change in loneliness is used as the measure for effectiveness in the cost-effectiveness analysis (CEA). Also in the responder analysis, a responder will be defined as a participant achieving a reduction of two points or more on the DJGLS at least once within the 12-month follow-up period.

As the EQ-5D-5L questionnaire is used to value a person’s health-related quality of life but might not capture all aspects of social well-being, we will perform an additional cost-capability analysis (CCA). Therefore, the ICECAP-A questionnaire will be used. The ICECAP-A questionnaire comprises additional aspects of well-being including dimensions beyond mere health and such as attachment, stability, achievement, enjoyment, and autonomy [31, 55]. These five dimensions are assessed on four levels resulting in a total of 1,024 capability states. For ICECAP-A, different value set exists [56–59]. We will use the original UK tariff as referred to by the University of Bristol [60]. After scoring a value for each of the five dimensions, the value for the overall capability state is calculated by summing them up. A capability state can have a value from 0 (no capability) to 1 (full capability). By multiplying capability values with the dwelling time in the capability state, years of full capability (YFC) are calculated [57]. The approach for calculating YFC is similar to calculating QALYs, however capability states are used instead of health states. The ICECAP-A questionnaire will be included in the trials in Barcelona and Prague.

Data from the EQ-5D-5 L [61], the DJGLS [52], and the ICECAP-A questionnaire [31] are collected at t0, t1, t2, and t3.

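### In Helsinki the EQ-5D-5L proxy behind the primary cost-utility analysis may be completed by the facilitators who deliver the intervention, which permits rating that differs by arm, and no planned analysis addresses it

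*Protocol article*

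**What the plan says.** Under Measurement and valuation of outcomes/ benefits, participants in Barcelona and Prague complete the EQ-5D-5L themselves, but "in Helsinki, the EQ-5D-5L questionnaire will be used as a proxy version filled out by facilitators or study nurses". Table 1 in the same section gives the data source for all sites as "Self-reported outcomes, proxy version by facilitators/ study nurses", with no rule by arm. The sentence after the Helsinki rule narrows it: "The proxy questionnaire is provided for participants who are unable to answer the original questionnaire due to cognitive impairments".

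Under Interventions and comparators, the facilitators are the people who deliver the programme: "Two trained facilitators are assigned to each group to support the group dynamics by fostering empowerment". During the sessions "the facilitators keep a diary, instruct the group, assure connectivity, and assist in ensuring compliance". Of the Helsinki controls the article says that "they do not participate in any further organized activities and receive no support from the FIN group or the facilitators".

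Under Health economic evaluation, the cost-utility analysis based on EQ-5D-5L utilities is the primary evaluation, and its ratio is interpreted first.

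**The concern.** A facilitator who completes the proxy form knows the allocation and is scoring the result of their own work. Because facilitators have no described role with Helsinki controls, facilitator-completed forms would be expected mainly in the intervention arm. If facilitators and nurses rate the same health state differently, part of the Helsinki QALY difference would be a rater effect.

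Proxy use is unlikely to be marginal. The article gives up the capability measure in Helsinki partly because a large proportion of participants may not be able to respond reliably.

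The two sentences on who is proxied raise a separate problem. If only those unable to answer are proxied, a participant whose cognition declines could move from self-report to proxy between visits, and the change of respondent would enter the QALY as a change in health. That is not linked to arm in itself, but it makes the data harder to interpret.

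**Working it through.** **What the text fixes and what it leaves open**

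| Question | Article |
|---|---|
| Who may complete the Helsinki proxy? | Facilitators or study nurses |
| Who delivers the intervention? | Facilitators, two per group |
| Do facilitators support Helsinki controls? | No |
| Which rater serves which arm? | Not stated |
| Who is proxied in Helsinki? | One sentence reads as everyone; the next as those unable to answer; Table 1 lists both self-report and proxy |

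**Do the planned analyses deal with it?** Under Statistical analysis, intention-to-treat keeps participants in their randomised arm, and adjustment is for baseline differences; neither touches a rater difference that arises at follow-up and follows the arm. Under Uncertainty analyses, the bootstrap resamples the data as rated, so a rater shift stays in every replicate. The listed sensitivity and scenario analyses cover winsorising, seemingly unrelated regression, exclusion of set-up costs and analysis without imputation. None concerns the rater, and the limitations in the Discussion do not mention it.

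**Size, as an illustration.** The article gives no figure for a rater effect, so there is no stated value to reproduce. QALYs are the area under the utility curve, taken here as trapezoids with visits at 0, 0.25, 0.5 and 1 year. The visit weights are:

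- t0: 0.25/2 = 0.125
- t1: 0.25/2 + 0.25/2 = 0.25
- t2: 0.25/2 + 0.5/2 = 0.375
- t3: 0.5/2 = 0.25

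They sum to 1, and t1 to t3 carry 0.875.

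Let b be the rater shift (facilitator minus nurse), q the difference between arms in the share rated by facilitators, and w the weight of the affected visits. With no shift at t0, bias in the QALY difference = w × b × q.

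| Assumed b | Assumed q | t1 only (w = 0.25) | t1 to t3 (w = 0.875) |
|---|---|---|---|
| 0.02 | 0.25 | 0.001 | 0.004 |
| 0.05 | 0.5 | 0.006 | 0.022 |
| 0.10 | 1 | 0.025 | 0.088 |

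Central row: 0.25 × 0.05 × 0.5 = 0.00625, and 0.875 × 0.05 × 0.5 = 0.0219. If both arms have the same mix of raters, q = 0 and the bias is 0.

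**Effect on a test.** The 316 participants per trial less 25% drop-out leave 316 × 0.75 = 237, or 118.5 per arm if allocation is 1:1 (assumed). With an assumed QALY SD of 0.15 to 0.25, the standard error is SD × √(2/118.5), that is 0.0195 to 0.0325. With no true effect, a two-sided 5% test would reject with probability 0.06 to 0.05 at a bias of 0.00625, and 0.20 to 0.10 at a bias of 0.0219 (smaller SD first).

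**The case against.** A reader might infer that rater and allocation are in fact confounded in Helsinki, with facilitators rating the intervention arm and nurses the controls. The documents do not support that. No sentence assigns raters by arm. The statement that controls get no support from facilitators describes their care, not who fills in their forms. Nurses may have rated everyone: the health economic questionnaire is self-reported or reported by the study nurse at every visit. Assessor rules may also stand in the published trial protocol, to which this article refers for trial conduct. All of this stands, and it limits the point to what the rule permits. It does not remove the point, because naming the deliverers of the intervention as raters is a choice stated in the article and not a detail left out.

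A reader might also infer that the bias favours the intervention and runs through all follow-up visits. The direction is plausible but not shown. The group programme is nine weekly sessions and aims at independence from the facilitator, and the first follow-up, at three months, marks its end. Nothing says that facilitators rate at 6 or 12 months, so the case limited to t1 must be shown beside the larger one.

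The sentences on who is proxied can be read together, the second qualifying the first, and Table 1 fits that reading. The fair complaint is unclear wording.

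Finally, the reach is limited. Only Helsinki is affected, and loneliness there is listed as self-reported, so the effect measure of its cost-effectiveness analysis is untouched.

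**Conclusion.** The concern holds as a weakness in the stated rule. The article allows the people who deliver the intervention to rate the outcome of the primary Helsinki analysis, has no safeguard by arm, and plans no analysis that would reveal or limit a rater effect. Whether ratings did differ by arm cannot be told from the article.

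Under the central assumptions (shift 0.05, half of the intervention arm, no control forms by facilitators), the spurious gain would be about 0.006 QALY if confined to three months and about 0.022 QALY if present at all follow-up visits. Over the wider assumed range it runs from about 0.001 to 0.088. The smaller values would hardly matter; the larger ones could change the Helsinki conclusion. Which applies depends on who completed the forms, and that should be established before the arms are compared.

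**What to change.** 1. **Forms still to be collected in Helsinki, if any.** Replace the choice between facilitators and study nurses with study nurses not involved in delivering the groups, in both arms. Keep one respondent mode, self or proxy, per participant where possible.
2. **Forms already collected.** Recruitment ended in September 2023, so this is probably most or all of them. Describe the raters as they were; do not rewrite the rule after the fact. Tabulate rater type and mode by arm and visit before any comparison by arm.
3. **Analysis.** Prespecify a Helsinki cost-utility sensitivity analysis that treats facilitator-completed forms as missing, handled under the approach in Sample size and missing data, and report it next to the as-collected result. It should not replace the base case: if facilitators rated most intervention-arm forms, little would remain to impute from, and that section does not fix one method for follow-up utilities. In that event, state that the Helsinki QALY difference cannot be separated from a rater effect.
4. **Wording.** Reconcile the two sentences on who is proxied, and Table 1 with them.

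The cost is a little extra analysis and a wider interval in the sensitivity analysis. Study nurses are already named as raters, so no new type of staff is needed, and no sample size changes.
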